### Recruitment

We will collaborate with non-governmental organizations and outpatient treatment centers in Vienna, Austria, that provide psychological and psychiatric help for treatment-seeking asylum seekers and refugees. These partners have agreed to inform help-seeking Afghan asylum seekers and refugees about our study as part of their initial contact with them giving them our contact information. Participants’ travel costs will be refunded for each assessment and treatment session. Each participant will receive monetary compensation for their involvement (€10; handed out at the 6-month follow-up assessment). As all participants are on a waiting list for professional mental health treatment, it is possible that some might receive treatment during the period of their study participation (i.e., before their 6-month follow-up assessment). As this is considered part of their usual treatment, we do not exclude participants if they receive additional treatment; however, considering the average waiting time of more than a year, we do not expect this in many cases. Information regarding received medical attention and mental health treatment will be gathered during follow-up assessments for both groups.

### Group allocation and blinding

The allocation ratio will be 1:1 with 60 participants per group (total *N* = 120). Participants will be randomly assigned to either group with random allocation software after the baseline assessment. The random numbers will be generated by an assistant who will not be involved in the assessments or in the treatment. The participants will be informed after the baseline assessment. The study will assessor-blind; that is, the psychologist conducting the baseline and follow-up assessments will be masked with regard to the allocated treatment arm (adapted PM+ vs. TAU).

### Statistical analyses

First, we will compare baseline scores between the treatment group and TAU group on all primary and secondary outcome measurements, using chi-squared tests and two-sample *t* tests, for categorical and continuous variables, respectively. In order to estimate significant changes over time as a result of the intervention for all primary and secondary outcome measures, we will employ hierarchical linear modelling (HLM). Analyses will be based on an intent-to-treat population, where critically HLM allows the number of observations to vary between participants and effectively handles missing data by calculating estimates of trajectories using maximum likelihood estimation. Time (linear and quadratic), treatment condition, and their interaction will be included in the models, where we will also examine how covariate factors such as age, biological sex, education level, and asylum status explain variance within the data. Here, similar models will be employed for the primary and secondary outcome measures, and we will conservatively correct for multiple comparisons where appropriate. Specifically, the level 1 model will characterize within-patient change over time, and the level 2 model will predict variation of within-patient change over time and between-patient variables.

We will also examine whether treatment success can be predicted from baseline clinical measures and individual differences using machine learning methods, including non-linear random forest regressions and linear ordinary least squares model with lasso regularization (OLS-LASSO).

In regard to qualitative data, interviews of the sub-sample will be transcribed verbatim and will be analyzed using thematic analysis [45]. The thematic analysis approach is a method for identifying, analyzing, and reporting themes within data. The in-depth interviews will be analyzed independently by two researchers, and inter-rater reliability will be calculated. The results from the interviews following the online training tool will be analyzed with the same methodological approach.

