### Sample size

Studies using the original PM+ manual so far have found small to large effects compared with TAU at 6 months post-treatment. Assuming an α error probability of 0.05 and a power (1-β error probability) of 0.80, we need a total sample size of 90 persons (45 persons per group) when testing for a medium effect (*f* = 0.3). We chose the more conservative approach and assumed only small effects of the treatment and thus aim to include 90 persons in the analysis. We expect a dropout rate of 25%. Taking this into account, we aim to include a total of 120 participants who will be randomly assigned to either the intervention arm (*n* = 60) or the TAU arm (*n* = 60). A subgroup of the intervention arm (*n* = 20) will be invited for in-depth interviews.

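### The primary model leaves the GHQ-28 baseline mean free to differ by arm although randomisation follows baseline; constraining it would gain precision, by an amount that depends on quantities the protocol does not give

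*Protocol article*

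**What the plan says.** The Statistical analyses section plans a hierarchical linear model, fitted by maximum likelihood in the intent-to-treat population, whose terms are "Time (linear and quadratic), treatment condition, and their interaction". The Primary outcome section has GHQ-28 measured at baseline, 7 weeks and 6 months, and the model is described as characterising within-patient change, so baseline is one of the modelled outcomes. On covariates, the section says "we will also examine how covariate factors such as age, biological sex, education level, and asylum status explain variance within the data". Baseline GHQ-28 is not named, and no equality of baseline means is stated. Similar models are planned for the secondary outcomes.

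The Group allocation and blinding section fixes the order of events: "Participants will be randomly assigned to either group with random allocation software after the baseline assessment".

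The Sample size section supplies the planning figures: "Assuming an α error probability of 0.05", "a power (1-β error probability) of 0.80" and, "when testing for a medium effect (*f* = 0.3"), the statement "we need a total sample size of 90 persons (45 persons per group"). It adds "We expect a dropout rate of 25"%, which leads to 120 randomised. It names no test, correlation or SD.

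**The concern.** With time zero at baseline, the treatment term in this model is the difference between arms before anyone has been treated. In a trial randomised after baseline, that quantity is known to be zero in expectation. Estimating it spends information on a known value, and the noise passes into the treatment-by-time effect. That effect then subtracts the whole of any chance baseline difference, whereas with equal SDs only a fraction rho of it is expected to carry forward to follow-up.

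What is at stake is precision. Only 90 participants are expected in the analysis, and the baseline score, which is usually the strongest predictor of the follow-up score, will already have been collected.

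**Working it through.** **1. The plan's own figure.** Inputs from the Sample size section: alpha 0.05, power 0.80, f = 0.3, 45 per arm, 25% dropout. With two groups d = 2f = 0.6. A two-group F test with noncentrality N f² = 90 × 0.09 = 8.1 has power 0.804, and 90 is the smallest even total that reaches 0.80. Then 90 / (1 − 0.25) = 120. Both figures reproduce. The test is inferred from this match; the protocol does not name it.

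**2. What the planned model estimates.** Three visits with an intercept, linear and quadratic time, treatment, and both interactions give three free means per arm. With complete data, the treatment-by-time effect at a follow-up visit is exactly the difference between arms in change from baseline.

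**3. Variances.** Let s be the SD, equal at baseline and follow-up (assumed), and rho the baseline-to-follow-up correlation (assumed).
- Change from baseline: 2s²(1 − rho)
- Baseline constrained or adjusted: s²(1 − rho²)
- Reduction: 1 − (1 − rho²) / [2(1 − rho)] = (1 − rho)/2

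This gives 35%, 25% and 15% at rho 0.3, 0.5 and 0.7. Simulation with 20,000 trials per value and 45 per arm gave 34%, 24% and 13%. Both estimators centred on the true −0.60, so the target is the same.

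**4. How the reduction moves when the assumptions change.** The next table uses generalised least squares for three visits at 0, 7 and 26 weeks with equal variances and correlations. The dropout pattern is assumed: per arm, 45 complete, 8 missing 6 months only, 7 with baseline only. Entries are variance reductions for the 6-month effect.

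| Setting | rho 0.3 | rho 0.5 | rho 0.7 |
|---|---|---|---|
| Both time terms interact, complete data | 35% | 25% | 15% |
| Both time terms interact, 25% dropout | 29% | 20% | 12% |
| Linear interaction only, complete data | 30% | 20% | 11% |
| Linear interaction only, 25% dropout | 27% | 17% | 9% |

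Now let the baseline SD be k times the follow-up SD, with complete data and both interactions. The reduction is (k − rho)² / (k² + 1 − 2k·rho).
- k = 0.7, rho 0.3: 0.16 / 1.07 = 15%. At rho 0.5: 0.04 / 0.79 = 5%. At rho 0.7: 0%.
- k = 1.2: 47%, 40% and 33% at rho 0.3, 0.5 and 0.7.

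**5. Power.** This step assumes that d = 0.6 is in raw-score SD units, 45 completers per arm, equal SDs, and a two-sided 0.05 test (noncentral t, 88 degrees of freedom). The standardised effect is 0.6/√[2(1 − rho)] for change and 0.6/√(1 − rho²) with baseline constrained or adjusted.

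| rho | Change from baseline | Constrained or adjusted |
|---|---|---|
| 0.3 | 0.6/1.183 = 0.507, power 66% | 0.6/0.954 = 0.629, power 84% |
| 0.4 | 0.548, 73% | 0.655, 87% |
| 0.5 | 0.600, 80% | 0.693, 90% |
| 0.6 | 0.671, 88% | 0.750, 94% |
| 0.7 | 0.775, 95% | 0.840, 98% |

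At rho 0.5 the change SD equals the raw SD, because 2(1 − 0.5) = 1. That is why the change contrast meets the planned 80% at that value.

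**The case against.** A time-by-treatment hierarchical model is a standard, valid analysis of a randomised trial. The article condenses a fuller plan, and its covariate list is introduced as examples, so baseline GHQ-28 could still be added. This stands in part. The list leaves room for baseline but does not commit to it, and its stated purpose is to examine explained variance. The model terms themselves are stated, and they include a free treatment effect alongside the baseline measurement.

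The time coding and the extent of the interaction are also open. If time were centred at 6 months and both time terms interacted with treatment, the treatment coefficient would be the raw 6-month difference, and the change-score variance would not describe it. The baseline means would still be free, and using the baseline score would still help. If only linear time interacts, the gain is smaller, as shown above.

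A reader might infer a flat saving of 15% to 35%. The documents do not support that. It needs an assumed rho of 0.3 to 0.7, equal SDs, complete data and both interactions. The plan itself expects dropout, and entry on a positive RHS-15 screen could narrow the baseline SD.

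A reader might also infer that the trial is underpowered. That does not follow. The Sample size section does not say that f is in raw-score SD units. If f refers to the planned contrast, power with 45 per arm is 80% at every rho. Counting only 45 completers also ignores the planned use of all observations by maximum likelihood: under the assumed dropout pattern, power at rho 0.3 is about 70% for the change contrast and 84% with baseline constrained.

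**Conclusion.** The point holds as lost efficiency. The analysis as described is neither biased nor invalid, and a reader who took it to be so would go beyond the documents. Randomisation after baseline makes the baseline arm difference zero by design, and the stated model estimates it anyway. Constraining the baseline targets the same mean difference and, asymptotically, cannot lose precision.

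The size is conditional because the protocol gives neither rho nor SDs. Over an assumed rho of 0.3 to 0.7 with equal SDs, the variance reduction runs from 35% to 15% with complete data. It runs from about 29% to 12% under the assumed 25% dropout pattern, and from about 27% to 9% with that dropout if only linear time interacts. With complete data and a baseline SD of 0.7 of the follow-up SD, it is between about 15% and nothing; a wider baseline SD would raise it. The shortfall against 80% power arises only if f = 0.3 is in raw-score SD units and rho is below 0.5. The change is worth making because it helps across nearly all of this range and costs almost nothing.

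**What to change.** State in the Statistical analyses section that the primary GHQ-28 model constrains both arms to a common baseline mean: keep baseline in the outcome vector, drop the treatment effect at baseline, and keep the treatment-by-follow-up-visit terms for 7 weeks and 6 months. Apply the same form to each secondary outcome measured at baseline.

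This form is preferable to modelling only the follow-up scores with baseline as a covariate. That alternative drops participants with no follow-up score from the fitted data, whereas the constrained model keeps every randomised participant in the likelihood, in line with the planned intent-to-treat analysis.

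The cost is a change of wording. The data and the type of model are already planned, and the constraint uses no extra degree of freedom (baseline as a covariate would use one). It would also help to say whether f = 0.3 refers to raw scores or to the planned contrast, and which rho was assumed, so that the 80% power can be tied to the primary test.

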### Data monitoring

All serious adverse events (SAEs) that are reported spontaneously by the participants or observed by the investigators during the trial will be recorded by the research team and will be reported to the independent advisory board [46]. The chair of the advisory board will review SAEs within 72 h, and the research team will review all AEs regularly and, where necessary, respond appropriately. The consent process includes informing participants about whom they can contact if they experience adverse reactions (i.e., Kriseninterventionszentrum Wien [Crisis intervention center Vienna]). Depending on the nature of the adverse event, follow-up may require additional tests or medical procedures as indicated and/or referral to a general physician or medical specialist. All adverse events will be followed until specialist care (including referrals, additional tests, or medical procedures) is in place for the client or until a stable situation has been reached.

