### Objectives

The aims of this study are to evaluate the efficacy of a short-term transdiagnostic treatment protocol (adapted PM+) to address mental health problems and post-migration living difficulties for treatment-seeking Afghan asylum seekers and refugees who are on a waiting list for professional mental health treatment. This intervention aims to reduce typical symptoms of common mental disorders and associated distress via PMLDs.

We hypothesize that participants in the intervention group will show a significant reduction in general mental distress. Additional aims are to investigate the effectiveness of the intervention in (a) reducing symptoms of PTSD and complex PTSD, (b) alleviating the burden associated with PMLDs, (c) improving refugee’s quality of life, and (d) investigating the participants’ subjective experience and tolerance of the intervention.

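### The recording rule names serious adverse events, while review and follow-up cover all adverse events, so non-serious and transient events need not be logged or reportable by arm

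*Protocol article*

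**What the plan says.** Three duties are set out in the Data monitoring section of the protocol article.

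- Recording, together with reporting to the independent advisory board: "All serious adverse events (SAEs) that are reported spontaneously by the participants or observed by the investigators during the trial will be recorded".
- Review: the chair of the board looks at serious events within 72 h, and "the research team will review all AEs regularly and, where necessary, respond appropriately".
- Follow-up: "All adverse events will be followed until specialist care (including referrals, additional tests, or medical procedures) is in place for the client", or until the situation is stable.

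The Objectives section lists as aim (d) "investigating the participants’ subjective experience and tolerance of the intervention". The article's qualitative source on participants' experience is the in-depth interviews. The Sample size section says of them: "A subgroup of the intervention arm (*n* = 20) will be invited for in-depth interviews". The Statistical analyses section says that "interviews of the sub-sample will be transcribed verbatim and will be analyzed using thematic analysis".

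**The concern.** The section treats serious events and adverse events as different things: serious events go to the chair of the board, and adverse events in general go to the research team. The recording sentence can therefore not be read as using the narrower term loosely for the wider one. Two staff members could each comply with a different sentence and produce different data. One would log serious events alone. The other would log everything, because review and follow-up require it.

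This matters because the intervention consists of six talking sessions. Plausible harms of such a treatment, such as distress after a session, a short-lived worsening, or stopping because the content is upsetting, would usually not meet a definition of seriousness. If they are logged by some staff and not by others, or not at all, the trial cannot give a trustworthy count of them in either arm. Events left unlogged cannot be reliably recovered later.

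**Working it through.** The article states no figure on this point, so the check is a comparison of its sections.

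**1. Scope of each duty in Data monitoring**

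| Duty | Events named | Who |
|---|---|---|
| Recording and reporting to the board | Serious, if spontaneously reported or observed | Research team |
| Review within 72 h | Serious | Chair of the board |
| Regular review | All adverse events | Research team |
| Follow-up to care in place or stability | All adverse events | Not stated |

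The last two rows need a list of non-serious events to work from. The first row does not provide one, and no other sentence in the article does.

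**2. What else would pick up harm, in both arms**

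- GHQ-28 at baseline, 7 weeks and 6 months, by blinded assessors (Primary outcome). The control arm is assessed at the same time points (Control condition).
- Health-care contacts and treatment received, gathered at follow-up for both groups (Additional measures; Recruitment).

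These show worsening that is present at a visit, and harm that led to contact with care. They do not show distress that came and went between visits, and they do not record why someone stopped attending.

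**3. What remains uncovered**

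Taking steps 1 and 2 together, the gap consists of events that are non-serious, have resolved by the next assessment, and led to no health-care contact, plus reasons for stopping. In the intervention arm the interviews may reveal some of these, but in 20 of 60 participants at most, and as themes, not counts.

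**4. Opportunity to be noticed**

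The recording sentence relies on spontaneous report or observation. Counting the scheduled contacts after randomisation, and leaving out the interviews:

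- intervention arm: 6 sessions + 2 follow-up assessments = 8
- control arm: 0 sessions + 2 follow-up assessments = 2

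Simply widening the recording sentence, without a common question at the common visits, would therefore give counts by arm that differ partly because one group is seen more often. This is why the fix ties the question to the 7-week and 6-month assessments.

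**5. Denominators**

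The Sample size section expects 25% dropout. If that falls equally on both arms, about 60 × (1 − 0.25) = 45 per arm would be available for a by-arm table at follow-up. That is enough for a descriptive comparison, and the number assessed has to be shown next to each count.

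**The case against.** The strongest reply is that the recording sentence describes the escalation route for serious events and is not an exhaustive rule. It does not contain the word only. The duties to review and follow all adverse events presuppose that non-serious ones are captured somewhere, and a journal article commonly leaves the log itself to the full protocol. Much of this stands. It rules out the claim that non-serious harm is excluded from the data. It does not remove the mismatch: the article does not stay silent on the scope of recording but states one, and that scope is narrower than the duties that depend on it.

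A reader might also infer that non-serious harm goes wholly unmeasured. The article does not support this, because the GHQ-28 and health-care contacts are collected in both arms.

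A reader might further infer that aim (d) fails because the control arm gives no tolerance data. That does not follow either. The aim concerns tolerance of an intervention that the control arm does not receive, it is not worded as a between-arm comparison, and it is paired with subjective experience, for which interviews are planned. The article does not say expressly that the interviews cover tolerance, so that link is an inference.

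Finally, it is tempting to put a confidence limit on an event not seen in 20 interviews. The interviews are qualitative and are not planned to estimate a rate, so such a limit would have no clear meaning here.

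**Conclusion.** The inconsistency is real and the sentences must be reconciled. As the recording sentence is written, non-serious events need not be logged and cannot be dependably reported by arm. The consequence is limited to non-serious and transient events and to reasons for stopping. Serious events have a stated route, sustained worsening is measured in both arms, and no primary or secondary efficacy analysis changes. Its frequency cannot be estimated from the article.

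The conclusion rests on two assumptions: that staff may follow the recording sentence literally, and that no wider rule in the full protocol, which is not shown, overrides it. If such a rule exists, the remedy is to bring the article's wording into line with it. The change is worth making because it is cheap and improves what the trial can say about harm.

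**What to change.** 1. Reword the recording sentence so that it covers all adverse events, serious and non-serious, on one log for both arms, with serious events flagged for the existing 72 h review.
2. Ask every participant the same open question about unwanted events since the last assessment at the 7-week and 6-month assessments. Keep events noted at sessions or reported spontaneously on the same log, marked by source, so that the by-arm comparison can rest on the answers to the common question.
3. Report, by arm, the number of participants with at least one adverse event, with the number asked.
4. Tabulate, by arm, how many participants have a worse GHQ-28 than at baseline at 7 weeks and at 6 months, with the number assessed. This needs no new data. Some participants will score worse by chance, so the table should be read as a comparison of arms and not as a count of harmed people.

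The cost is a change of wording, a short log, two descriptive tables and a few minutes within each 90-minute follow-up assessment, with no new visits. One caution: an answer may reveal the allocation to the masked assessor, so the question is best placed after the outcome questionnaires. Recruitment began in June 2019, so participants assessed before the change will not have been asked, and the tables should state from which date the question applied.
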